#### Multivariate analysis

Logistic regression will be applied to determine the independent effects of age, gender, ASA classification, body mass index, reason ESRD, time of surgery, medical history, previous PD catheter insertion and previous abdominal surgery on catheter survival.

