## Abstract

**Background:**

Peritoneal dialysis (PD) is an effective treatment for end-stage renal disease. It allows patients more freedom to perform daily activities compared to haemodialysis. Key to successful PD is the presence of a well-functioning dialysis catheter. Several complications, such as in- and outflow obstruction, peritonitis, exit-site infections, leakage and migration, can lead to catheter removal and loss of peritoneal access. Currently, different surgical techniques are in practice for PD-catheter placement. The type of insertion technique used may greatly influence the occurrence of complications. In the literature, up to 35% catheter failure has been described when using the open technique and only 13% for the laparoscopic technique. However, a well-designed randomized controlled trial is lacking.

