### Study design

The LOCI-trial is a multicenter prospective single blinded, randomized controlled trial. The LOCI-trial has a pilot nature, as the study will generate data that should enable us to design a large multi-center randomised controlled trial comparing the laparoscopic PD insertion technique with the open technique.

The design of this protocol is in accordance with the CONSORT guideline [20]. We have stratified per center, PD in the past and previous episodes of peritonitis. The study has started on May 24^th ^2011 and the duration will be approximately 1.5 years. This study compares laparoscopic and open PD catheter insertion. In total 100 patients will be included in the study. Approval of the Medical Ethical Committee Erasmus MC, Rotterdam, The Netherlands, was obtained.

Randomisation will take place after endotracheal intubation, by means of a web-based computer programme with supervision of the study coordinator. This computer programme will generate the randomisation sequence. The patient will be blinded for the operation technique in the postoperative period. The wounds will be covered with a standard pattern of bandages [21]. All patients will fill out questionnaires (the Short-Form 36 (SF-36), EuroQol (EQ-5D) and a Visual Analogue Scale (VAS) for pain) until 6 months postoperatively. (Table 1)

**Table 1 T1:** Time schedule for filling out the questionnaires

Time of evaluation	VAS	EuroQol	SF-36
Preoperative	X	X	X
Postoperative			
Day 0	X		
Day 1	X		
Day 2	X		
Day 3	X	X	
Week 1	X	X	
Week 2	X	X	
Week 4		X	X
Week 6			X
Week 8			X
Week 12		X	X
Week 26		X	X

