### Sample size calculation

At present, we do not have sufficient data to perform a power analysis. Therefore, this pilot study will include two groups of 50 patients. We anticipate that these 100 patients will be sufficient to indicate a difference in technical failure rate at 6 weeks. We do not expect to find significant differences in secondary end points in this relatively small number of patients. In order to be able to include the number of required patients, this study will take place in multiple hospitals. Based on the outcome of this pilot study, we will design a larger multicenter randomized controlled trial, including a large number of patients based on a power calculation.

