### Outcome measures

#### Primary outcome

The percentage of functioning CAPD catheters at 6 weeks postoperatively. This is defined by not having an indication for catheter removal or revision for:

• An in- and/or outflow restriction. Outflow restriction is defined as an outflow time longer than 30 minutes, and urokinase treatment has failed.

• Refractory peritonitis, relapse peritonitis or fungal peritonitis, as described in the national guidelines defined by the Dutch Federation of Nephrology.

• Severe abdominal pain (VAS > 8) for 4 weeks.

• Pericanullar or subcutaneous leakage of peritoneal fluid not improving spontaneously within 5 weeks after catheter insertion.

• Tunnel- or exit-site infection not responding to treatment in 2 weeks (refractory infection).

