### Statistical analysis

#### Descriptive statistics

Categorical variables will be presented as numbers (percentages). Continuous variables will be presented as medians (ranges). Categorical variables will be compared with the Chi-square test. Continuous variables will be compared with the Mann-Whitney-U test. All analyses will be conducted using SPSS (version 17.0, SPSS Inc., Chicago, USA). A P-value <0.05 (two-sided) will be considered statistically significant.

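### The only multivariable model omits the randomised technique and two of the three stratification factors, and enters at least nine factors on about 24 expected failures

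*Protocol article*

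**What the plan says.** The Multivariate analysis section of the protocol article specifies a single model: "Logistic regression will be applied to determine the independent effects of age, gender, ASA classification, body mass index, reason ESRD, time of surgery", continuing with "medical history, previous PD catheter insertion and previous abdominal surgery on catheter survival". That makes nine factors. Laparoscopic versus open insertion is not one of them, and the outcome is given no time point.

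On randomisation, the Study design section states: "We have stratified per center, PD in the past and previous episodes of peritonitis". Previous catheter insertion in the model roughly covers the second of these three factors. Centre and previous peritonitis appear in no stated analysis.

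The technique comparison falls to the unadjusted chi-square test named under Descriptive statistics and Univariate analysis, applied to the primary outcome: "The percentage of functioning CAPD catheters at 6 weeks postoperatively". The same part of the article sets the threshold, "A P-value <0.05 (two-sided) will be considered statistically significant", with no allowance for multiple tests.

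On size: "Therefore, this pilot study will include two groups of 50 patients". The only failure rates given for both techniques are in the Abstract: "In the literature, up to 35% catheter failure has been described when using the open technique and only 13% for the laparoscopic technique".

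**The concern.** The primary question is whether technique changes the rate of malfunctioning catheters. The one adjusted analysis in the plan cannot speak to it, because technique is not in the model. A prognostic model that leaves out the factor the trial expects to matter is also misspecified for its own purpose.

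Randomisation was stratified, but no analysis uses the strata. If centre, earlier PD or earlier peritonitis predict failure, an unadjusted test discards the precision that stratifying was meant to provide, and tends to be conservative.

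The model is also large for the data. With so few failures per term, maximum-likelihood logistic regression exaggerates real effects. Nine or more tests at 5% each also make it quite likely that something is reported as an independent predictor by chance.

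**Working it through.** The article gives no event count and no power calculation ("At present, we do not have sufficient data to perform a power analysis"), so there is no figure of its own to reproduce. The check starts from its sample size and literature rates.

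**1. Model terms against stratification factors**

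| Item | In the logistic model? |
|---|---|
| Technique (randomised) | No |
| Centre (stratified) | No |
| PD in the past (stratified) | Roughly, through previous catheter insertion |
| Previous peritonitis (stratified) | No |

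**2. Expected failures and events per variable**

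Events = 50 × (open rate) + 50 × (laparoscopic rate), assuming no dropout. Only the first row uses the article's pair of rates; the others are assumptions to show the range.

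| Open / laparoscopic | Events | Events ÷ 9 |
|---|---|---|
| 35% / 13% | 17.5 + 6.5 = 24 | 2.7 |
| 25% / 13% | 12.5 + 6.5 = 19 | 2.1 |
| 20% / 10% | 10 + 5 = 15 | 1.7 |
| 35% / 35% | 17.5 + 17.5 = 35 | 3.9 |

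Nine terms is a minimum. If ASA class, cause of renal disease and medical history are coded in several categories, the count rises. For an assumed 12 terms, 24/12 = 2.0.

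**3. Chance of at least one false-positive predictor**

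For k independent tests at 5% the chance is 1 − 0.95^k:

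- k = 9: 37%
- k = 12: 46%
- k = 14: 51%

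Simulated logistic fits used 100 patients, about 24 failures and pure-noise covariates, with assumed distributions. They gave 37-39% with nine terms, 49% with 12 and 50% with 14. The rate per covariate was 5.4% with nine terms and 5.8% with 14. Multiplicity therefore explains most of the figure, and overfitting adds little to it. The 12- and 14-term figures count each category indicator as a separate test.

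**4. Overfitting and exaggeration**

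- Pure-noise covariates alone reached an apparent AUC of 0.70 (nine terms) to 0.75 (14 terms).
- With 14 terms, a true log-odds ratio of 0.69 was estimated at 0.89 on average (0.89/0.69 = 1.29), and at 1.04 when only significant results were kept (1.04/0.69 = 1.51).
- Fits failed or separated in 0.7% (nine terms) to 6.4% (14 terms) of runs.

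**5. What happens if technique is simply added to the list**

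The true log-odds ratio at 13% versus 35% is ln[(0.13/0.87)/(0.35/0.65)] = −1.28, an odds ratio of 0.28. With technique plus nine null covariates the mean estimate was −1.51 (1.51/1.28 = 1.18, an 18% inflation). With 12 terms the inflation was 25% (odds ratio about 0.20). With 14 covariate terms the mean was −1.64 (1.64/1.28 = 1.28). Adding technique without shortening the list would replace one problem with another.

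**6. Size of the proposed model**

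Technique, PD in the past and previous peritonitis make three terms: 24/3 = 8 events per term. The number of centres is not given. If they are pooled into three groups (an assumption), two more terms make five: 24/5 = 4.8. That is better than 2.7 but still thin, hence the penalisation.

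**The case against.** The strongest reply is that the model is prognostic by its own description. It sets out to find patient and surgical factors that affect catheter survival and does not claim to estimate an adjusted effect of technique. The trial question is answered by the chi-square test, which is valid in a randomised comparison. This stands: a reader might infer that the primary analysis is invalid or the trial question unanswered, and the article does not support that.

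A reader might also infer that the reported predictors would be largely spurious. They would not: each covariate's error rate stays near 5-6%, and most null factors would correctly be non-significant. The 18-25% inflation in step 5 should not be read as bias in the planned analysis either, because it describes a model that the article does not contain. It is only a warning about the obvious repair.

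The 24 failures are a projection. The 35% is an upper literature figure, neither rate carries a time horizon, and 35%/13% is not the most favourable case for event count: 35% in both arms gives 35. The Background reports comparative trials without significant differences, so similar rates are possible. Even so, 35 events leave fewer than four per variable.

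Nor does the article say that risk factors from this regression will feed the next trial. It says only that the pilot's outcome will inform that trial's design and power calculation.

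Finally, modelling detail might be left to a fuller document. That does not dispose of the point. The article fixes a specific covariate list, and its Discussion says the statistical methods to be used are in the protocol. The issue is a stated method, not an absent one.

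**Conclusion.** The point holds for a secondary analysis and leaves the primary comparison intact. The stated model gives no adjusted effect of technique and leaves out centre and previous peritonitis, although randomisation was stratified on both. It rests on about 2.7 events per variable, or 1.7 to 3.9 over assumed counts of 15 to 35. Its estimates would be overfitted and imprecise, with true effects exaggerated (by roughly 30% in the simulated 14-term example). The chance of at least one false-positive predictor is about 37% with nine terms and 50% with 12, mostly because multiplicity is not addressed.

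The event counts assume no dropout and the literature rates; fewer failures at 6 weeks would make matters worse. The simulated figures depend on assumed covariate distributions and coding. The low ratio of events to terms does not. The plan should be changed, and the change is cheap.

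**What to change.** 1. Pre-specify one adjusted model for a functioning catheter at 6 weeks, containing technique plus the stratification factors: centre (small sites pooled), PD in the past and previous peritonitis. Use Firth penalisation if the data are sparse.
2. Report the technique effect from that model with its 95% CI, alongside the chi-square test.
3. Do not repair the existing model by adding technique to the nine factors.
4. Drop the nine-factor model, or label it exploratory, with penalised estimates, a stated time point for catheter survival and no significance claims.
5. Define time of surgery. If it means operating time, technique can affect it after randomisation, so keep it out of any model that estimates the technique effect.

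The cost is a few sentences of wording, with no change to recruitment or data collection. The downside is that the list of independent predictors is lost or downgraded, but about 24 failures could not support that list.

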### Data collection and access to personal data

The operative data will be filled in immediately after the operation by the operating surgeon via an online case record form. The follow-up data will be collected by the study coordinator, using the same system. The case record forms are only accessible by logging in to a specially designed website (http://www.locitrial.nl). All personal data is coded into numbers (1 to 100). Data will be verified at six months postoperatively by comparing the patient records with the completed case record forms manually. The coordinating investigator and the principal investigator are the only persons who have access to the coding system. According to hospital guidelines, all data are imported into a secured database on a server of our institution and are managed by the coordinating investigator. At the end of the trial all data is analysed in collaboration with the trial statistician.

## Discussion

In the literature, case-series suggest that the laparoscopic insertion technique is to be preferred over the open technique. A higher incidence of exit-site infections in the open group (6.3-41% [22-25]) versus the laparoscopic group (2.5-18% [26,27]) is reported, as well as a higher incidence of catheter migration in the open group (7.6-17.1% [22,25,28] versus 1.3-5.4% [26,27,29]. No differences have been described between open and laparoscopic PD catheter insertion regarding the incidence of peritonitis, 2.9-31% [22-25] and 2.5-31% [26,27,30], respectively. Important outcome measures such as cost-effectiveness and quality of life have hitherto not been investigated. To evaluate the true value of laparoscopy in PD-catheter insertion, a well designed randomized controlled trial, such as the LOCI trial, is warranted.

To improve the reporting of this randomized controlled trial, the methods of this protocol are in adherence with the latest CONSORT statement (items 3-12 of the CONSORT checklist [20]). This study is designed as a randomized controlled trial (item 3) and the eligibility criteria for participants are specifically mentioned in the methods section (item 4). The surgical techniques are described in detail, so replication will be possible (item 5). Primary and secondary outcome measures are pre-defined (item 6). This is a pilot-trial and therefore a sample-size calculation is not required at this point (item 7). The methods of patient inclusion, the methods of randomization and the mechanism to conceal the sequence until interventions will be assigned, is described in detail (item 8-10). This study is single-blinded and the methods to achieve this are described in detail (item 11). The statistical methods which will be used for the analysis of the results are present in this protocol (item 12).
